## Abstract

**Background:**

N-acetylcysteine (NAC), which is specifically involved in airway mucus clearance and antioxidation, is recommended by the treatment guideline for non-cystic fibrosis bronchiectasis (NCFB). However, there is little clinical evidence of its long-term efficacy concerning quality of life (QoL) and exacerbation in patients with NCFB. In addition, the influences of NAC on airway bacterial colonization, chronic inflammation and oxidative stress in NCFB are also unclear.

**Methods:**

NINCFB is a prospective, multicentre, double-blind, randomised, placebo-controlled trial that will recruit 119 patients with NCFB and randomly divide them into an NAC group (*n* = 79) and a control group (*n* = 40). Participants in the NAC group will receive 600 mg oral NAC twice daily for 52 weeks, while patients in the control group will receive 600 mg placebo twice daily for 52 weeks. The information at baseline will be collected once participants are enrolled. The primary endpoints are the changes in St George’s Respiratory Questionnaire scores and the number of exacerbations in 52 weeks. The secondary endpoints are the 16S rRNA of sputum and the levels of inflammatory factors and oxidative stressors in sputum and serum. Other data related to radiography, lung function tests, number of oral and/or intravenous antibiotic therapies and adverse events (AEs) will also be analysed. Further subgroup analysis distinguished by the severity of disease, severity of lung function, airway bacterial colonization and exacerbation frequency will be performed.

**Discussion:**

The objective of this study is to determine the long-term efficacy of NAC on QoL and exacerbation of NCFB and to explore the effectiveness of NAC for antibiosis, anti-inflammation and antioxidation in NCFB. The study results will provide high-quality clinical proof for the revision and optimization of treatment guidelines and for expert consensus on NCFB treatment.

**Trial registration:**

The trial was registered on the Chinese Clinical Trial Register at April 11, 2020 (chictr.org.cn, ChiCTR2000031817).

## Background

The worldwide prevalence and health care burden of non-cystic fibrosis bronchiectasis (NCFB) have been increasing rapidly in recent years [1–3]. In China, nearly 1.2% of individuals over 40 years old are diagnosed with NCFB, and its morbidity is positively correlated with age [4]. Effective therapy and management of this disease are urgently needed.

NCFB, caused by various primary pathogenic processes, such as pathogenic organism infection, immune deficiency and congenital defects [5], is a chronic purulent lung disease causing irreversible bronchial dilation and bronchial wall thickening [6, 7], which greatly complicates its treatment and management [8]. Accumulation of sputum, chronic airway inflammation and repeated exacerbations are the main characteristics of NCFB [9, 10]. Research has shown that 50% of patients with NCFB have two or more exacerbations annually, and one in three require hospitalization [11]. Continual expectoration and frequent exacerbations have significantly troubled patients and greatly reduced their quality of life (QoL) [12]. Consequently, improving airway mucus clearance, reducing exacerbation and enhancing QoL are the significant treatment goals of NCFB [13].

N-acetylcysteine (NAC), which provides the sulfhydryl group that can break the disulfide bond of the glycoprotein polypeptide chain in the phlegm to reduce the viscosity of sputum [14, 15] and can act as a direct reactive oxygen species (ROS) scavenger to regulate the redox status in the cells [16], has been recommended by treatment guidelines of chronic pulmonary disease for airway mucus clearance [15]. However, there are only a few clinical investigations on its specific efficacy for NCFB, and the long-term effectiveness of NAC for patients’ QoL has not been reported either. In addition, although NAC was determined to have antibacterial properties [17, 18] and the ability to interfere with signal pathways of inflammation [19] and oxidative stress [20] in chronic obstructive pulmonary disease (COPD), these capabilities in NCFB are still unclear [13].

A randomised controlled trial conducted by Qi, Q., et al. in 2014 demonstrated that NAC can decrease the number of exacerbations of patients with NCFB [21], but it did not evaluate the QoL of patients or further explore the antibiosis, anti-inflammation and antioxidation of NAC for NCFB.

Given all of these findings, we designed this clinical trial (NINCFB) to test our hypothesis that NAC can play a significant role in antibiosis, anti-inflammation and antioxidation to reduce exacerbations and enhance QoL of patients with NCFB.

## Methods

### Study objective

The key objectives of NINCFB are as follows:Determine the long-term efficacy of NAC in improving QoL of patients with NCFB.Determine the long-term effecacy of NAC in reducing exacerbation frequency of patients with NCFB.Explore the activities of NAC in antibiosis, anti-inflammation and antioxidation for the treatment of NCFB.Evaluate the long-term influence of NAC on clinical manifestations, pulmonary function and computed tomographic imaging features of patients with NCFB.Evaluate the long-term adverse effects of NAC on patients with NCFBConducting a subgroup analysis to investigate the different effectiveness of NAC on NCFB with different severities and causes, such as pathogen infection, immune deficiency and congenital defects.Trace biomarkers that can be predictors of NCFB progression or indicators of NAC efficacy.

### Study design and intervention

NINCFB is a prospective, multicentre, double-blind, randomised, parallel, placebo-controlled trial studying NCFB in Chengdu city, Sichuan Province of China (Fig. 1). It is recruiting 119 patients with NCFB from 6 hospitals located in Chendu city and randomly (2:1) assigning these patients into an N-acetylcysteine (NAC) group (*n* = 79) and a control group (*n* = 40). Participants in the NAC group will be given oral N-acetylcysteine (produced by Hainan Zambon Pharmaceutical Co., Ltd.; national medicine permission number: H20000471; 600 mg, twice daily) for 52 weeks, while the control group will receive oral placebo (produced by Hainan Zambon Pharmaceutical Co., Ltd.; 00520C0; 600 mg, twice daily) for 52 weeks. All the participants will be followed up throughout the intervention period and will be required to provide relevant information about their demography, aetiology, symptomatology, bacteriology and radiography. The results will be analysed and presented in other papers. Study enrolment started on 3 March 2021 and is expected to be completed on 31 December 2024.

**Fig. 1 Fig1:**
[figure not shown]
Flow chart summarising the study procedure

### Study setting

Chengdu city is the largest city in Sichuan Province, located in southwestern China, and has a residential population of 21.2 million. We included 6 hospitals in Chengdu based on willingness to participate (Table 1). All the patients meeting the inclusion criteria from each hospital are recommended to attend and complete the trial in the Good Clinical Practice Center of West China Hospital of Sichuan University.

**Table 1 Tab1:** Hospitals participating in the trial

Research Centers in Chengdu City	
West China Hospital of Sichuan University	
Chengdu Fifth People’s Hospital	
Chengdu Sixth People’s Hospital	
Chengdu University Affiliated Hospital	
Nuclear Industry 416 Hospital	
General Medical 363 Hospital	

### Study participants

Both outpatients and inpatients who satisfy the inclusion criteria and do not meet the exclusion criteria will be invited into the study. All participants are required to sign informed consent forms before trial enrolment. The original documents will be preserved by themselves, and copies will be archived with the case report forms (CRFs).

#### Inclusion criteria

(1) 18 years or older at enrolment; (2) having diagnosed with non-cystic fibrosis bronchiectasis (NCFB) by high-resolution computed tomography (HRCT) scans; (3) a forced expiratory volume in 1 s (FEV1) ≥ 30% of its predicted value in pulmonary function tests; (4) having had at least two pulmonary exacerbations requiring oral antibiotics or at least one pulmonary exacerbation necessitating intravenous antibiotics in the year before enrolment; and (5) having been in a stable state of NCFB for at least 4 weeks prior to randomisation.

#### Exclusion criteria

(1) Bronchiectasis due to cystic fibrosis; (2) having received systemic antibiotics treatment within 4 weeks before the follow-up; (3) primary diagnosis of COPD or asthma; (4) having diagnosed with allergic bronchopulmonary aspergillosis (ABPA), active nontuberculous mycobacterium (NTM) infection or active tuberculosis; (5) comorbidity with severe cardiovascular, digestive, kidney diseases and malignant tumours; (6) history of surgeries in the past 3 months prior to enrolment; (7) known allergy to NAC; (8) pregnancy or lactation or plan for pregnancy in the next 52 weeks; (9) history of prior macrolide use of more than 1 week; (10) poor compliance (any patient who has poor memories to take medicine and has no caregiver or family for supervision is considered as poor compliance.).

### Outcome measures

All outcome measures will be recorded at baseline and during the intervention period (Table 2).

**Table 2 Tab2:** Study main measures and outcomes to be collected

Variable	Baseline (0-week)	1-month follow-up (4-weeks)	3-month follow-up (12-weeks)	6-month follow-up (26-weeks)	9-month follow-up (38-weeks)	12-month follow-up (52-weeks)
Primary Endpoint 1						
SGRQ scores	X	X	X	X	X	X
Primary Endpoint 2						
Number of exacerbations during the follow-up		X	X	X	X	X
Secondary Endpoints						
16S rRNA sequencing of sputum	X			X		X
Inflammatory factors	X			X		X
Oxidative stressors	X			X		X
Other Variables						
Clinical signs and symptoms	X	X	X	X	X	X
Transcutaneous regional oxygen saturation	X	X	X	X	X	X
BSI scores	X	X	X	X	X	X
mMRC dyspnea scores	X	X	X	X	X	X
HRCT grade, n (%)	X					X
Number of lesion lobes, n (%)	X					X
FEV1/FVC%	X			X		X
FEV1%	X			X		X
Number of exacerbations 12-months before the enrollment and during the trail	X	X	X	X	X	X
Time to first exacerbation		X	X	X	X	X
Time to second exacerbation		X	X	X	X	X
The longest duration of exacerbation in the last year	X					
The longest duration of exacerbation during the follow-up		X	X	X	X	X
Number of oral antibiotic therapies 12-months before the enrolment and during the trail	X	X	X	X	X	X
Number of intravenous antibiotic therapies 12-months before the enrolment and during the trail	X	X	X	X	X	X
Number of systemic glucocorticoid utilization12-months before the enrolment and during the trail	X	X	X	X	X	X
Number of hospitalization 12-months before the enrolment and during the trail	X	X	X	X	X	X

X means items should be evaluated or detected at the current follow-up

#### Primary endpoints

The primary endpoints of the NINCFB are quality of life (St George’s Respiratory Questionnaire, SGRQ scores) and the number of exacerbations during the follow-up period. The SGRQ, a comprehensive questionnaire to estimate pulmonary symptoms and living conditions, is commonly used to assess a patient’s quality of life [22, 23] and has good psychometric properties for the NCFB [24]. Exacerbation of NCFB is defined by the British Thoracic Society as acute deterioration (usually over several days) with worsening local symptoms (cough, increased sputum volume or change in viscosity, increased sputum purulence with or without increasing wheezing, breathlessness, or haemoptysis) and/or systemic upset [25]. This study has two variables designed to determine whether the long-term effectiveness of NAC achieves the treatment goal of NCFB (Table 2).

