### Data collection

Two clinical researchers at West China Hospital of Sichuan University will collect the data and make appointments for the following dates at the end of the first meeting to promote participant retention. A monitoring team consisting of 2 respiratory physicians and 1 investigator will verify and revise the results, it is independent from the sponsor and competing interests. Peripheral blood tests, electrocardiogram (ECG) readings, spirometry and HRCT scans for all the subjects will be conducted by laboratory experts and radiologists at West China Hospital of Sichuan University. All data collected both on paper and in electronic archives will be marked with a study identification number to confirm participants and will be stored in a locked cabinet and hospital computer system. Once recorded, the data will be locked to prevent changes. Missing data because of “no-shows” will be coded as incomplete. Access to the identified information sets will be limited to the study authors.

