### Statistical analysis

The resulting data will then be analysed with SPSS V.26 by statistical experts. Primary outcomes of each group will be compared by Student’s t test (t test) or the Wilcoxon rank-sum test after calculating its normal distribution and will be expressed in terms of the mean, standard deviation (SD) or median to indicate the long-term efficacy of NAC for NCFB. The comparison between the NAC group and the control group in terms of 16S rRNA and the levels of inflammatory factors and oxidative stressors will be of vital importance. In addition, NINCFB will also use the t-test, chi-square test and Wilcoxon rank-sum test to evaluate baseline discrepancy and other variables. Regression analysis and the correlation coefficient may confirm the predictors of disease progression and indicators of NAC efficacy.

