### Sample size

We calculate the sample size required for the evaluation of primary outcome-1 (SGRQ scores) and primary outcome-2 (number of exacerbations) respectively. As NAC is effective in reducing sputum of patients with NCFB in clinical practice, we design a ratio of 2:1 for the sample size of intervention group to control group in this study so that two-thirds of enrolled patients could receive effective treatments. For the SGRQ score, we regard mean difference (MD) of 6 points of SGRQ score as the smallest clinically important difference between two group with a standard deviation (SD) of 8.5 used in the calculation, according to the previous report of NAC on patients with COPD [35–37]. Based on 90% power with a two-sided significance level of 5%, a sample size of 64 for intervention group and 32 for control group is needed as calculated by the software PASS 15. In addition, assuming 20% of patients in each group may drop out or lose data integrity, we need to recruit 79 in the intervention group and 40 in the control group. For the number of exacerbation, we regard MD of 0.7 times of exacerbation per year as the smallest clinically important difference between two group with a SD of 1 used in calculation, according to the published study of NAC on patients with postinfection or idiopathic bronchiectasis [21]. Considering 20% dropout, we also need to recruit 79 patients in NAC group and 40 patients in placebo group (α = 0.05, 1 - β = 0.9). Taken together, this study eventually aims to enroll 119 participants, of them, 79 in the NAC group and 40 in the placebo group.

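### Primary endpoint 2 is a raw exacerbation count tested without regard to time observed, although the trial is sized per year and expects 20% dropout; how partly observed patients enter is not stated

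*Protocol article*

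**What the plan says.** - **Endpoint.** The Primary endpoints section and Table 2 define primary endpoint 2 as "the number of exacerbations during the follow-up period". The abstract gives the intended window: "the number of exacerbations in 52 weeks". No denominator of observed time is given.
- **Test.** Under Statistical analysis: "Primary outcomes of each group will be compared by Student’s t test (t test) or the Wilcoxon rank-sum test". The choice between the two depends on a check of normality.
- **Sizing.** Under Sample size: "we regard MD of 0.7 times of exacerbation per year as the smallest clinically important difference", "with a SD of 1 used in calculation". Recruitment is inflated "assuming 20% of patients in each group may drop out or lose data integrity".
- **Incomplete follow-up.** The Data collection section says only that data missing through no-shows "will be coded as incomplete". The Adverse events section has patients leave the study once an adverse event is judged causally related.
- **Related counts.** Antibiotic courses, systemic glucocorticoid use and hospitalisations are also recorded as numbers during the trial (Table 2), and the Other variables section calls them incidences.

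**The concern.** The plan targets an annual difference and expects a fifth of patients to be incompletely observed, yet it names tests that see only each patient's total. Suppose a patient leaves at week 12 without an exacerbation. If that count enters as it stands, the patient is scored the same as one who completes 52 weeks without an exacerbation. If the patient is left out, 12 weeks of valid observation are lost and the comparison is confined to completers. The article does not say which applies.

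This goes beyond detail that an article would leave to an analysis plan, because the article itself fixes both the raw count and tests that take no account of exposure. At stake is one of the two primary results. It could be diluted, shifted by dropout that differs between arms, or based on a selected subset.

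**Working it through.** **1. The plan's own sample size.** Inputs from the Sample size section: difference 0.7, SD 1, allocation 2:1, α = 0.05 (two-sided, as stated for SGRQ), power 0.90, dropout 20%.

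Control n = (1 + 1/2) × (1.96 + 1.2816)² × 1² / 0.7² = 1.5 × 10.51 / 0.49 = 32.2; NAC n = 64.3. Dividing by 0.8 and rounding up gives 41 and 81, close to the stated 40 and 79. Power with 64 and 32 evaluable is 0.899 (normal) or 0.893 (noncentral t). The stated size is reproduced to within two per arm, and the sizing arithmetic is not at issue.

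**2. Expected raw-count difference if partial counts enter.** Assumptions, because the article gives neither control rate nor dropout timing: exit is uniform over the year and unrelated to exacerbations. With dropout proportion d, mean follow-up is 1 − d/2 years, and

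expected difference = λ_C(1 − d_C/2) − λ_N(1 − d_N/2).

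- 20% in both arms: 0.90 × 0.70 = 0.63, whatever the control rate. With no drug effect the expected difference is 0.
- No drug effect, 1.65 per year in both arms, 27.5% NAC v 5% placebo: 1.65 × (0.975 − 0.8625) = 0.186. Overall dropout is (79 × 0.275 + 40 × 0.05)/119 = 20%, so the total matches the plan but the split does not.

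Over a range of control rates:

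| Dropout, NAC v placebo | True difference | 1.5/year | 2.0/year | 2.5/year |
|---|---|---|---|---|
| 20% v 20% | 0.70 | 0.63 | 0.63 | 0.63 |
| 25% v 10% | 0 | 0.11 | 0.15 | 0.19 |
| 30% v 0% | 0 | 0.23 | 0.30 | 0.38 |
| 10% v 40% | 0.70 | 0.44 | 0.37 | 0.29 |

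**3. Type I error (simulated, 79:40, no drug effect).** The rate analysis here is a log rate ratio on person-time with robust variance. Overdispersed means a gamma-mixed count with variance μ + μ²/2.

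- 20% in each arm: 4.8–5.8% on raw counts, which is nominal.
- 27.5% v 5%, 1.65 per year: about 13% on raw counts if Poisson and about 9% if overdispersed, against 5–6% for the rate analysis.
- 25% v 10%, 2 per year, mild overdispersion (frailty variance 0.1): 7.6% (t) and 7.9% (rank-sum), against 5.3%.
- 30% v 0%, same assumptions: 17.5% and 19.4%, against 5.5%.

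**4. If partly observed patients are excluded.** In the 27.5% v 5% case, completers-only testing kept type I error near 5%, because exit was unrelated to exacerbations. When 15% of patients left after each exacerbation (true rates 1.3 v 2.0 per year, 800 trials), the completer difference was 0.48–0.60 and the raw-count difference 0.50–0.55, against 0.64–0.72 for the rate.

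**5. Power (1.3 v 2.0 per year, 20% uniform dropout in each arm).**

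| | t test, raw count | Rank-sum, raw count | Rate analysis |
|---|---|---|---|
| Poisson | 74% | 67% | 78% |
| Overdispersed | 51% | 41% | 53% |

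These powers are below 90% mainly because the simulated SD exceeds the plan's SD of 1 (√2.0 = 1.41 for a Poisson count at 2.0). They serve only to compare methods.

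**The case against.** **The plan may not use truncated counts at all.** A reader might infer that shortened follow-up will be read as fewer exacerbations. The article does not say so. Inflating about 64 and 32 evaluable patients to 79 and 40 suggests that dropouts may be treated as not evaluable, and the abstract fixes a 52-week window. This stands: truncation is one of two readings. The other has its own weakness, reliance on completers.

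**Exclusion is not the only alternative within the named tests.** This also stands. Events divided by time observed can go into a rank-sum test; doing so gave type I error of 5.1% and 4.9% in the 27.5% v 5% case. But the article does not call for it.

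**Inflated type I error is not shown under the plan's own assumption.** With 20% in each group the error is nominal and the effect is only diluted. A false difference needs more or earlier exit in one arm. Withdrawal for related adverse events makes that possible, but nothing in the document shows that it will happen.

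**A large loss of power is not shown either.** Setting rank-sum on raw counts against the rate analysis suggests a gap of 11–12 points. Against the t test, which the plan also names, the gap is 2–4 points. Most of the rest is the choice of test: with no dropout, rank-sum on overdispersed counts still trailed the rate analysis, 47% against 57%.

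**A fuller plan may already settle this.** It may, and event timing is partly recorded (time to first and second exacerbation in Table 2). But a rate model there would differ from the test stated in the article, and the two would have to be reconciled.

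**Conclusion.** The concern holds in a limited form and should be fixed. The article pairs a raw count with tests that ignore exposure, sizes the trial on an annual difference, expects 20% dropout, and leaves open how partly observed patients enter.

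- **If they enter as they stand:** dilution from 0.70 to 0.63 under equal dropout with nominal type I error; under dropout that differs by arm, a false difference (about 0.19 and 9–13% type I error at 27.5% v 5%).
- **If they are excluded:** valid type I error when exit is unrelated to exacerbations, but discarded data, and bias when exit follows exacerbations.

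The direction of the dilution and of the false difference follows from the formula. The sizes rest on assumed control rates (1.5 to 2.5 per year), dispersion and uniform exit times, none of which the document gives. The documents do not support saying that the planned analysis will produce a false benefit, or that it forfeits much power.

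**What to change.** Define primary endpoint 2 as the exacerbation rate from randomisation to last contact or week 52, whichever comes first, in all randomised patients. Analyse it by negative binomial regression with log(time observed) as offset. Report the rate ratio with 95% CI, together with the implied difference per year so that the result can be read against the 0.7 used for sizing. Treat the antibiotic, glucocorticoid and hospitalisation counts the same way. Specify all this before unblinding, which the article defers until every participant has finished follow-up.

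**Cost.** This is mainly wording. Each patient's last contact date must be in the analysis file, and the planned software (SPSS 26) can fit the model. The primary effect measure becomes a ratio, whereas the trial was sized on a difference in means.

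**Limit.** The offset corrects for time observed. It does not remove bias when exit depends on exacerbation risk that was not observed, so reasons for and timing of exit should be reported by arm.
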